## Abstract

The benefits of Pilates have been extensively researched for their impact on muscular, psychological, and cardiac health, as well as body composition, among other aspects. This study aims to investigate the influence of the Pilates method on the learning process, motor control, and neuromuscular trunk stabilization, specifically in both experienced and inexperienced practitioners. This semi-randomized controlled trial compares the level of experience among 36 Pilates practitioners in terms of motor control and learning of two Pilates-based skills: standing plank and side crisscross. Data will be collected using various assessment methods, including abdominal wall muscle ultrasound (AWMUS), shear wave elastography (SWE), gaze behavior (GA) assessment, electroencephalography (EEG), and video motion. Significant intra- and inter-individual variations are expected, due to the diverse morphological and psychomotor profiles in the sample. The adoption of both linear and non-linear analyses will provide a comprehensive evaluation of how neuromuscular structures evolve over time and space, offering both quantitative and qualitative insights. Non-linear analysis is expected to reveal higher entropy in the expert group compared to non-experts, signifying greater complexity in their motor control. In terms of stability, experts are likely to exhibit higher Lyapunov exponent values, indicating enhanced stability and coordination, along with lower Hurst exponent values. In elastography, experienced practitioners are expected to display higher transversus abdominis (TrA) muscle elasticity, due to their proficiency. Concerning GA, non-experts are expected to demonstrate more saccades, focus on more Areas of Interest (AOIs), and shorter fixation times, as experts are presumed to have more efficient gaze control. In EEG, we anticipate higher theta wave values in the non-expert group compared to the expert group. These expectations draw from similar studies in elastography and correlated research in eye tracking and EEG. They are consistent with the principles of the Pilates Method and other scientific knowledge in related techniques.

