### 2.6. Statistical Analyses

This study seeks to contribute to the explanation and understanding of phenomena related to Pilates using a mixed quantitative and qualitative methodology. For the statistical treatment and linear analysis, IBM SPSS Statistics 28.0 software (IBM Corporation, New York, NY, USA) will be used, with a level of significance at 5% (*p* < 0.05). Descriptive statistics, including the calculation and analysis of the mean and standard deviation, will be conducted for all variables. If validation of the normality and heterogeneity assumptions of the sample are assured, then the analysis of variance ANOVA [56] will be used with multiple comparisons of means performed using the post-hoc Tukey test to verify the differences between the groups [57]. The effect size (ES) for ANOVA test is interpreted using the following criteria: no effect (ES < 0.04), minimum effect (0.04 ≤ ES < 0.25), moderate effect (0.25 ≤ ES < 0.64), and strong effect (ES ≥ 0.64) [58]. Apart from the effect size, the power (π) of the corresponding test will also be presented [59]. Pearson’s correlation analysis is defined to establish the associations between the studied variables [60].

While linear measures are useful for quantitative data analysis, taking a different perspective, non-linear data analysis is employed to characterize the collected data. This type of analysis provides insights into the organization of data within a system, offering a more nuanced understanding of the underlying patterns and structures in the dataset. The regularity, variability and complexity of the signal and the motor system in different levels of response [61,62] can lead to a larger understanding of the collected data. In fact, sample entropy can tell the amount of uncertainty attending the order of an output signal, i.e., predictability [63]. On the other hand, the Lyapunov exponent will be used to analyze the periodicity and regularity of the signal and the motor system in a time series [61]. Finally, the Hurst exponent [64,65] will be used to measure the tendency of the values of the motor system along a time scale. To proceed with the computation of the time series, the program will use UPATO [66].

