## 3. Results

In general, we anticipate both intra-individual and inter-individual differences that may result in statistically significant variations in the studied variables. This expectation considers the sample’s considerable diversity and variability in terms of morphological characteristics and psychomotor profiles.

Given that we have adopted both linear and non-linear analyses, which will provide a more comprehensive assessment of how the sample has evolved in terms of neuromuscular structures over both space and time, it is expected that the results may exhibit both quantitative and qualitative aspects. This will enable a mixed and more robust analysis of the applied methodology. For instance, within the context of non-linear analysis, we expect that results will show higher entropy in the expert groups when compared to non-experts. Regarding stability, the expert group is expected to exhibit higher Lyapunov exponent values compared to other groups, accompanied by lower Hurst exponent values. In the context of elastography, we anticipate that the elasticity of the transversus abdominis (TrA) muscle will be higher in experienced practitioners compared to those with less experience, both within the same group over time and when comparing across groups.

In terms of gaze behavior, results should reveal a greater number of saccades, more Areas of Interest (AOIs), and less time spent in fixation for the non-expert sample. This is because expert practitioners are assumed to have a more efficient mastery of gaze behavior.

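### The abstract reads a higher Lyapunov exponent in experts as better stability, but a larger exponent means lower local dynamic stability

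*Protocol article*

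**What the plan says.** The Abstract gives both a direction and a meaning: "experts are likely to exhibit higher Lyapunov exponent values, indicating enhanced stability and coordination, along with lower Hurst exponent values".

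Section 3 (Results), which sets out the expected findings, repeats the direction: "Regarding stability, the expert group is expected to exhibit higher Lyapunov exponent values compared to other groups, accompanied by lower Hurst exponent values". It places the prediction under stability but does not state separately that higher means more stable.

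Section 2.6 (Statistical Analyses) describes the purpose of the index: "the Lyapunov exponent will be used to analyze the periodicity and regularity of the signal and the motor system in a time series". It gives no sign convention, no direction and no claim about stability.

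The companion prediction in the Abstract is "Non-linear analysis is expected to reveal higher entropy in the expert group compared to non-experts, signifying greater complexity in their motor control", and section 2.6 explains that "sample entropy can tell the amount of uncertainty attending the order of an output signal, i.e., predictability".

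**The concern.** The Lyapunov exponent measures how quickly small differences between neighbouring states grow. The Abstract attaches the opposite meaning to a high value. Neuromuscular stabilization of the trunk is part of the objective at the end of section 1 and returns in section 4, and of the three non-linear indices this is the one the article reads as stability. If the stated reading is carried into the report, any difference found between experts and the other groups will receive the wrong stability label.

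**Working it through.** The article states no figure for this index, so there is nothing numerical to reproduce. The check is of direction.

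**Inputs.** The predicted direction and meaning come from the Abstract and section 3, and the stated use of the index from section 2.6. The definition of the exponent is standard. The numerical values of lambda below are illustrations and do not come from the article.

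**Step 1: definition.** For two trajectories that start a small distance d0 apart, the separation after time t is approximately

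d(t) = d0 × exp(lambda × t).

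For fixed d0 and t, d(t) increases with lambda over its whole range. If lambda is positive, a larger value means faster growth of a perturbation. If lambda is negative, a higher (less negative) value means slower decay. In both cases higher means less locally stable.

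**Step 2: small example.** Per unit of time, lambda = 0.5 gives exp(0.5) = 1.65-fold growth and lambda = 1.0 gives exp(1.0) = 2.72-fold growth. The higher exponent belongs to the less stable system.

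**Step 3: numerical check on a known system.** For the logistic map, lambda was computed as the mean of log|f′| over 100,000 iterations. Separately, a perturbation of 1e-8 was followed for 15 iterations:

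| lambda | perturbation after 15 steps, relative to its start |
|---|---|
| −0.22 | 0.035 |
| +0.35 | about 349 |
| +0.49 | about 3,305 |
| +0.69 | about 37,981 |

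The negative exponent goes with decay, and among the positive ones divergence rises with the exponent.

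**Step 4: what the stated reading does with each possible result.**

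| Experts' exponent versus other groups | What the index shows | Reading under the Abstract |
|---|---|---|
| Higher | Lower local dynamic stability | Better stability; hypothesis supported |
| Lower | Higher local dynamic stability | Counted against the hypothesis |

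**Step 5: is the scale inverted anywhere?** Sections 2.4 and 2.6, the Abstract and section 3 contain no rescaled, reciprocal or sign-changed exponent. A use aimed at periodicity and regularity is compatible with the ordinary definition.

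**Step 6: what does not change.** Section 2.6 plans ANOVA with Tukey comparisons, which have no built-in direction. Section 2.2 sizes the study on a two-tailed test with alpha 0.05, 90% power and d = 1.39. None of this depends on how the exponent is interpreted.

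**The case against.** The strongest reply is that these are expectations, not decision rules. The planned tests are non-directional, group means would be reported correctly whatever the Abstract says, and the wording could be corrected at any time before publication. The explicit misreading occurs once, in the Abstract; section 3 only implies it. All of this is right, and it confines the problem to interpretation. It does not remove it, because the Abstract says what a high value indicates and nothing elsewhere corrects that.

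A second reply is that skilled movers may show functional variability, so a higher exponent in experts is a reasonable prediction. That could justify the direction, but as complexity or adaptability. It does not justify the stability label.

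A reader might also infer three stronger points that the article does not support:

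- *Section 2.6 misstates the sign.* It does not. It names a purpose and no direction, so it needs an addition, not a reversal.
- *The entropy and Hurst predictions are further errors.* They are not. Higher entropy, a higher exponent and a lower Hurst exponent can be read together as more complex, less predictable movement, and the Abstract reads entropy as complexity. Only the stability label on the Lyapunov exponent is wrong.
- *The exponent is the trial's trunk-stability endpoint.* No section makes it a primary outcome. Sections 1, 2.4.2 and 2.4.6 link trunk stability to ultrasound, elastography and video motion.

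**Conclusion.** The concern holds as an error of interpretation in the Abstract, echoed in section 3. Test results, alpha, power and sample size are untouched. The effect is a reversal of the stability statement attached to this one index: a higher exponent in experts would be presented as better stability, and a lower one would count against the hypothesis. No numerical effect on this trial can be given, since the article reports no expected exponent values.

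The conclusion assumes that the exponent is computed with its usual sign, as a rate of divergence. The article gives no reason to think otherwise. If an inverted scale is intended, it would have to be stated.

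**What to change.** Before the data are analysed:

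1. In the Abstract and section 3, state that a larger Lyapunov exponent means lower local dynamic stability.
2. Commit to one hypothesis in both places: either experts are more stable and so have a lower exponent, or experts have a higher exponent read as greater complexity or variability, in line with the higher-entropy prediction, and not as stability.
3. Add one sentence to section 2.6 giving the direction in which the exponent will be interpreted.

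The cost is a few sentences. No new data, change of sample size or change of test is needed.

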## 1. Introduction

The Pilates Method was developed by Joseph Hubertus Pilates in the early 1920s. It aims to holistically improve physical conditioning by focusing on the dualism of the body and mind. This technique targets trunk stability, strength, flexibility, posture, and breathing. The method is based on six principles: center, concentration, control, precision, fluidity, and breathing. It can be practiced alone or in groups, with or without equipment such as a reformer, Cadillac, arcs, Swiss balls, or bands [1,2].

The popularity of Pilates has led to an increase in research on its potential benefits [3]. However, the current limitations include (i) great sample heterogeneity; (ii) predominance of female sex; (iii) absence of effective assessment of long-term effects; (iv) variation in types of intervention (e.g., with or without equipment); and (v) the study of the cost–benefit ratio [4]. To address these limitations, we propose a multifactorial analysis approach based on dynamic, ecological, and cognitive perspectives [5,6]. Our study incorporates echography, electroencephalography, gaze behavior, and kinematic data to provide a broader understanding of the effects and potential benefits of Pilates in the current context [7].

Research on Pilates has primarily focused on its effects and benefits on core muscles [8]. With the large number of techniques and muscles assessed with ultrasound imaging echography and electromyography, the results have varied between the positive effects of this method and the absence of influence on core stabilization muscles [9,10,11]. In this matter, our study focuses on the following set of four muscles: rectus abdominis (RA), obliquus internus abdominis (IO), oblique externus abdominis (EO) and transversus abdominis (TrA). Despite some debate around the inclusion of muscles within the “core”, our chosen combination incorporates specific muscle groups and the diaphragm as they play a crucial role in forming a framework essential for generating intra-abdominal tension. This tension not only helps to stabilize the spine but also holds great significance in terms of human movement and displacement [12]. As muscle elasticity has a strong association with muscle tension, in our study we will add elastography (SWE) to 2D ultrasound (ECG) in an attempt to introduce new data with more precision regarding the advantages of Pilates and trunk stability [13].

The influence of Pilates practice on neuro-muscular and cognitive function is interesting to address. Thus, research on physical activity using EEG signals, combined with nonlinear methods, will lead to new horizons in brain function research [14,15]. Recent studies point to advantages to cognitive performance in athletes compared to non-athletes [16], and it will be pertinent to obtain this knowledge in other types of activities and physical activity levels. In fact, new technologies and devices can use EEGs to study simple movements, introducing the possibility of investigating new experimental designs [17,18,19].

The gaze behavior associated with motor imagery obtained from mirror images may provide information regarding the motor control, learning speed and movement quality [20,21,22]. In activities with precise movements, such as dance, Pilates, or martial arts, the impact of the presence of a mirror and the gaze behavior of the practitioners still needs research [23]. Furthermore, the output of quality of movement, particularly if associated with other data, could be very useful for obtaining a clearer glimpse of these phenomena [24].

The objective of this study is to investigate how the Pilates method affects the learning process, motor control, and neuromuscular stabilization of the trunk, specifically in experienced and inexperienced practitioners. Secondly, it aims to identify differences in strength and muscle recruitment among the four selected muscles that we are studying. Finally, we aim to build a pattern or map of brain waves and gaze behavior, which will be created according to the practitioner’s level of experience and length of practice.

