#### Eligibility Criteria

The sample for the experienced group will be selected from a local Pilates studio. Participants must have more than six months of practice, with more than 1 h of practice per week [27]. The non-expert group will be composed of subjects who must not have had any Pilates practice in the last three months. For the control group, in addition to not practicing any form of Pilates in the last three months, we also require that they not practice any form of Pilates during the study. These subjects will be allowed to maintain their physical activity routines or create new routines if body and mind activities are not included (yoga, body balance, tai-chi, among others). All groups will be composed of 13 participants between 30 and 50 years of age. The exclusion criteria are pregnancy and medical contraindications to practicing physical exercise [29].

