### 2.3. Intervention

The expert group will maintain their normal Pilates activity (at least once per week/60 min) in their usual facilities. The only addition to their regular routines will be the two Pilates skills (standing plank and the side crisscross) introduced and evaluated in our studies. All instructors involved in these facilities will have specific training to be able to teach and supervise these two new skills (four hours).

These two exercises will be performed in a type of sliding machine called a Standing Machine; participants will be able to perform the exercises in various positions, adding some instability, but particularly in orthostasis. In the plank, participants maintain a straight back and then flex and extend the feet for eight cycles (Appendix C—Table A2). In the side crisscross exercise, the participant maintains a lateral position while a crossing of limbs is done repeatedly for fifteen cycles (Appendix C—Table A3). The Standing Machine is patented pending number No 118908 in National Institute of Industrial Property.

All instructors will have POLESTAR^®^ Pilates training completed between 2011 and 2015. The non-expert group will start a weekly program in one of the Pilates studios participating in this study. This group has a weekly standardized session (55 min average) according to Appendix B—Table A1. These participants perform two laps around the circuit, performing 8 to 10 repetitions in each station, performing the standing plank on the first lap and the side crisscross on the second.

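### The objective asks for an effect of Pilates in experienced practitioners, but no planned contrast can isolate one

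*Protocol article*

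**What the plan says.** The Introduction gives the first objective as to "investigate how the Pilates method affects the learning process, motor control, and neuromuscular stabilization of the trunk, specifically in experienced and inexperienced practitioners". The Abstract words the aim in the same way, as the influence of the method in both kinds of practitioner. Section 2.1 describes something different: a comparison of levels of experience.

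Three groups of 13 are planned (Eligibility Criteria):

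- **Experts** are chosen from a studio because they already practise: "Participants must have more than six months of practice, with more than 1 h of practice per week". During the study, "The expert group will maintain their normal Pilates activity (at least once per week/60 min) in their usual facilities". For all of them, "The only addition to their regular routines will be the two Pilates skills" (section 2.3).
- **Non-experts**: "The non-expert group will be composed of subjects who must not have had any Pilates practice in the last three months". Then, "The non-expert group will start a weekly program in one of the Pilates studios participating in this study" (section 2.3). That programme includes the two skills.
- **Controls** are recruited "in addition to not practicing any form of Pilates in the last three months", and "we also require that they not practice any form of Pilates during the study".

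The Results section expects transversus abdominis elasticity to be higher with experience, both longitudinally within a group and between groups.

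**The concern.** An effect of Pilates in a population needs a comparison in which Pilates exposure differs among people of that population. The objective names experienced practitioners as one of its two populations, yet all experts have the same exposure: usual sessions plus the two skills. The group without Pilates does not come from that population.

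What is at stake is the conclusion, not the data. An expert v control difference, or a change within experts, could be read as an answer to the stated objective for experienced people. The first mixes prior experience, self-selection into Pilates and current practice. The second mixes continued practice, two new exercises and retesting. The longitudinal expectation in the Results section makes the second reading more than theoretical.

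**Working it through.** The point is structural, and no sample-size figure decides it. The check is to set out who is exposed to what, and then to ask what each contrast varies.

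**Inputs.** Entry rules and group size (13 each) come from Eligibility Criteria; exposure during the study comes from section 2.3 and, for controls, from Eligibility Criteria.

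**Step 1: groups by experience at entry and Pilates during the study.**

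| | Pilates during the study | No Pilates during the study |
|---|---|---|
| Recruited as experienced | Experts (13) | none (0) |
| No Pilates in the last three months | Non-experts (13) | Controls (13) |

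One of the four cells is empty, and it is the one needed for an effect in experienced people.

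**Step 2: what each comparison varies.** Three groups give 3 × 2 / 2 = 3 pairwise contrasts, and there is also the experts' own change.

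| Comparison | Experience at entry | Pilates during the study | What it can show |
|---|---|---|---|
| Non-expert v control | same three-month rule | differs | effect of the programme, if allocation is randomised |
| Expert v control | differs | differs | experience and current practice, not separable |
| Expert v non-expert | differs | both practise, in different sessions | difference by experience, mixed with programme |
| Expert change over time | no comparator | constant | continued practice, new skills and retesting together |

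Count: 1 of the 3 pairwise contrasts varies exposure under a common entry rule; 0 of the 3 vary it among experienced people.

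**Step 3: can another planned feature fill the empty cell?**

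- The mirror factor (section 2.1, Table 1) changes the exercise condition, not exposure to Pilates.
- The ANOVA with Tukey comparisons (section 2.6) compares the groups that exist. It cannot supply one that does not.
- The semi-randomised label does not help for experts, since their experience is the reason for their selection.

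A statistical analysis plan could not repair this either, because it concerns which groups are recruited.

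**Step 4: how far the remaining contrast carries.** The article does not state that non-experts and controls are allocated at random. Table 2 also defines non-experts differently from Eligibility Criteria (by never having practised or by limited earlier practice) and has no row for controls, so the common entry rule rests on Eligibility Criteria alone. The twelve-week interval is stated for the ultrasound measurements (section 2.4.1), whereas the programme in Table A1 runs to weeks 7–8.

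**The case against.** The best reply is that the objective is loosely worded and the study is simply a comparison by expertise. Much of the text supports this. Section 2.1 and the Abstract's design sentence speak of comparing experience levels. Table 1 lists level of experience as the independent variable. The two exercises are chosen to be new to everyone, so learning can be watched in both experts and novices. The third aim is a map by experience and length of practice. The entropy, Lyapunov, Hurst and gaze expectations are all between-group. On this reading less experienced people are the intended comparator.

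What stands: this is what the design can deliver, and it limits the remedy to rewording. It does not remove the mismatch, because the Abstract and Introduction ask how the method affects both populations, and the elasticity expectation includes change within a group.

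Three stronger readings are tempting, and the documents do not support them:

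- A reader might infer that the controls are inexperienced people. Eligibility Criteria ask only for three months without Pilates, so a lapsed practitioner could enter. They are still not recruited as experienced.
- A reader might infer that the article already concludes there is an effect in experts. Its Conclusions section makes no such claim and speaks only of different expertise levels.
- A reader might infer that non-expert v control is a clean causal contrast. That depends on randomisation, which the article does not state.

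**Conclusion.** The concern holds in this form: the stated objective goes beyond the design for one of its two named populations. No experienced person is in a Pilates-free group by design (0 against 13 experts), and none of the three pairwise contrasts isolates an effect of Pilates in experienced people. Expert contrasts are non-randomised comparisons by experience level, and expert change is uncontrolled.

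This rests on reading the objective as its words stand, as an effect of the method in each population, and on the group definitions in Eligibility Criteria and section 2.3. It does not depend on the length of follow-up or on group size. No bias in a result has been quantified, and the documents give no basis for doing so. The planned data remain usable for comparisons by experience and, subject to how they are allocated, for the programme question in non-experts v controls. The change is worth making because it fixes what the trial may conclude.

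**What to change.** Reword the objective in the Abstract and Introduction to agree with section 2.1, in two parts.

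- **(a) Non-expert v control:** change over the intervention, for outcomes measured at both times (ultrasound at the initial assessment and twelve weeks, as stated). Call it an effect of the programme only if allocation between these two groups is randomised, and say so; otherwise call it an association.
- **(b) Experts v the less experienced groups:** differences associated with experience level, reported as associations.

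Report change within experts, including the elasticity expectation in the Results section, as descriptive. Make no claim in the eventual reports of an effect of the method in experienced practitioners.

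Cost: wording only, with no added participants or measurements. The downside is a narrower claim. Keeping the present objective would instead require an experienced comparator group, which is a change of design.
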